### 2.3. Ethical Approval

The current protocol has been reviewed and approved by the Scientific Ethics Committee of the Faculdad de Ciencias e del Deport de la Universidad da Extremadura, Spain (approval number: N°244/2024, 3 October 2024), and was developed following the Declaration of Helsinki for work with humans.

### 2.4. Instruments and Procedures

#### 2.4.1. Procedures

The intervention study was structured into several sequential phases to ensure methodological rigor and alignment with the study objectives: (i) SR—A comprehensive literature review was conducted to synthesize the current evidence on the effects of PA, organized sports, and structured training programs on MC in children; (ii) Program Design—the training protocol was developed based on the findings of the SR, incorporating best practices and evidence-based guidelines targeting fundamental motor skill development; (iii) Program Promotion—communication strategies will be employed to inform and engage the stakeholders, including the parents, coaches, and athletics club, about the program’s purpose and benefits; (iv) Definition of Procedures and Objectives—clear operational procedures and objectives for the intervention will be established to ensure fidelity in implementation and alignment with the research aims; (v) Participant Selection and Group Allocation—the sample will be defined, and the participants will be randomly assigned to either the athletics training group (IG_A) or the athletics training plus multi-activity group (IG_B); (vi) Baseline Assessment (T0)—an initial assessment will be conducted to establish the participants’ pre-intervention motor competence and anthropometric measures; (vii) Program Implementation—the 12-week training program will be administered to both intervention groups under controlled conditions; (viii) Post-Intervention Assessment (T1)—a final evaluation will be conducted 12 weeks later to assess the changes and outcomes related to the intervention; and (ix) Data Analysis and Interpretation—the collected data will be statistically analyzed to determine the effectiveness of the intervention, followed by a discussion and formulation of conclusions.

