## 2. Materials and Methods

### 2.1. Study Design

This study follows a randomized, controlled experimental design with parallel groups (1:1 allocation ratio), aimed at evaluating and comparing the effects of two types of training protocols on MC in children aged 6 to 10 years. This methodology is used considering the conclusions of the systematic review and the fact that the main researcher is an athletics coach.

The participants will be ecologically assigned into one of two intervention groups, depending upon the training schedule chosen by their parents, according to their availabilities, and being given no prior indication of which of the two programs will function on which schedule: (i) Intervention Group A (IG_A) will receive athletics-based training exclusively, three times per week for 12 consecutive weeks, with each session lasting 60 min; and (ii) Intervention Group B (IG_B) will receive a combined program consisting of athletics-based training twice per week and one additional session per week involving a complementary activity (gymnastics, handball, or motor games), also over 12 weeks and with 60 min sessions.

All the participants will undergo MC assessments at two times: (i) at baseline (T0), prior to the beginning of the intervention; and (ii) at post-intervention (T1), immediately following the 12-week training period.

The post-intervention evaluations will take place three days after the final training session, always in the afternoon, to ensure consistency in the testing conditions. Figure 1 illustrates the participant flow and intervention timeline for the trial.

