## 3. Outcomes

The assessments will be conducted at the Main Stadium of Leiria, [name]. We will use a gym prepared for gymnastics training. It is a large, well-equipped space that provides an atmosphere of concentration and comfort during testing. The MC assessment will occur on a Tuesday (i.e., three days after the last session—Saturday). In addition, assessments will take place during the training session period, meaning that IG_A will be tested at 17h30 and IG_B at 18h30. Given the spatial, human, and material conditions, it is possible for children from the same group to take the tests simultaneously, facilitating the process. Before carrying out the tests, the research group will provide the children with as much information as possible to avoid any doubts and answer all their questions clearly.

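### Baseline motor competence is scheduled after group allocation with no masking of assessors described, so T0 can be scored by staff who already know each child's arm

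*Protocol article*

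**What the plan says.** Section 2.4.1 (Procedures) introduces its list with "The intervention study was structured into several sequential phases to ensure methodological rigor and alignment with the study objectives". Phase (v) is "Participant Selection and Group Allocation—the sample will be defined, and the participants will be randomly assigned" to one of the two groups. Phase (vi) is "vi) Baseline Assessment (T0)—an initial assessment will be conducted to establish the participants’ pre-intervention motor competence and anthropometric measures". Phase (vii) is the 12-week programme.

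Section 2.1 (Study Design) places T0 only in relation to training: "at baseline (T0), prior to the beginning of the intervention". It also says that children enter a group "depending upon the training schedule chosen by their parents, according to their availabilities", and that families are not told beforehand which programme runs on which schedule.

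Section 2.4.4 has the research team, trained beforehand, administer the KTK3+. It does not mention masking to group. Section 3 (Outcomes) states that "assessments will take place during the training session period, meaning that IG_A will be tested at 17h30 and IG_B at 18h30". The sentence before it dates the test as three days after the last session, which is T1.

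Section 4 plans a 2 (groups) × 2 (time points) mixed ANOVA with r = 0.50, α = 0.05 and 18 children per group. It names no baseline covariate.

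**The concern.** Baseline is the one assessment that can be made blind to arm at almost no cost, because nobody can know a child's arm before the arms exist. The listed order gives this up.

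Once allocation is done, an assessor who knows the arm can, without intending to, instruct, encourage or count differently. The article states an expectation: hypotheses (iii) and (iv) in the Introduction predict that IG_B will do better, and Sections 2.1 and 5 say that the main researcher is an athletics coach. A slightly lower T0 in IG_B, or a slightly higher one in IG_A, would look like a larger gain in IG_B.

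At stake is the group-by-time effect, on which hypotheses (iii) and (iv) rest.

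**Working it through.** **Order of events.** Section 2.4.1 gives allocation (v), then T0 (vi), then training (vii), in a list declared to be sequential. Section 2.1 puts T0 before training, which agrees with that order and does not move T0 ahead of allocation. Nothing else in the text does so either. Figure 1, the timeline, is not available in the text reviewed.

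**How a T0 error enters the analysis.** With two groups and two time points, the group-by-time F test is equivalent to a two-sample t test on D = T1 − T0. If T0 in one arm is shifted by b through knowledge of the arm, the between-arm difference in mean D shifts by b in size, with opposite sign.

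**Inputs.** n = 18 per group, r = 0.50 and α = 0.05 come from Section 4. The SD is set to 1 at both time points. The shift b is an assumption, because the article gives no figure for it; the range shown is 0.1 to 0.3 SD.

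**Formulas.**

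- SD of change = SD × √[2(1 − r)] = √[2 × 0.5] = 1.00 SD.
- Standard error of the difference in mean change = 1.00 × √(2/18) = 0.333 SD.
- Noncentrality δ = b / 0.333. Degrees of freedom = 36 − 2 = 34. Two-sided critical t = 2.032.
- Rejection probability with no true effect = P(|t′| > 2.032), where t′ is noncentral t with 34 degrees of freedom and noncentrality δ.

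| Assumed T0 shift b | δ | Two-sided type I error |
|---|---|---|
| 0 | 0 | 5.0% |
| 0.1 SD | 0.3 | 6.0% |
| 0.2 SD | 0.6 | 9.0% |
| 0.3 SD | 0.9 | 14.1% |

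A normal approximation gives 6.0%, 9.2% and 14.7%.

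**Comparison: T0 as a covariate.** The bias becomes r × b = 0.5b, and the standard error becomes √(1 − r²) × √(2/18) = 0.866 × 0.333 = 0.289 SD. By the normal approximation the type I error is then about 5.3%, 6.4% and 8.1% for the same three shifts. Adjustment weakens the problem but does not remove it, and it is not the analysis that Section 4 states.

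**The case against.** **The size is hypothetical.** No shift is documented. The KTK3+ items are counts of steps, jumps, platform moves and catches (Section 2.4.4), and the assessors are trained beforehand. This stands: the percentages show what a given shift would do, not that one will occur. Counted items limit the room for scoring bias, but instruction and encouragement still depend on the assessor.

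**Families do not know the programme when they choose.** Section 2.1 says so, and it is a real safeguard on the children's and parents' side. The text does not say when they learn it. The point therefore concerns mainly the staff.

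**A reader might infer that T0 is held in each arm's own training slot.** The plural in "assessments will take place during the training session period, meaning that IG_A will be tested at 17h30 and IG_B at 18h30" allows this reading, but the paragraph dates only T1 and nothing fixes the hour of T0. The point rests on the order in Section 2.4.1 and does not need this inference.

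**A reader might infer that the order of phases is what prevents balancing on baseline.** That goes too far. Section 2.1 lets the parents' choice of schedule set the arm, so an earlier T0 would balance nothing by itself. T0 also remains available for adjustment in the analysis.

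**A reader might infer that children lost between allocation and T0 vanish from the record.** The article does not say this. Such a child has been allocated and can be counted, although without a baseline score.

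**Moving T0 to common sessions could introduce a bias.** If T1 stayed split by arm and T0 did not, a time-of-day effect would be present only at T1 and would pass into the change score. This objection is sound, and it shapes the fix.

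**Conclusion.** The concern holds in a limited form. The article places T0 after allocation and describes no masking of the assessors, so the baseline half of every change score is open to error that depends on arm. The planned test takes up such an error in full.

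The consequence depends on a shift that the article neither reports nor rules out. From 0.1 to 0.3 SD, the type I error rises from 5% to between about 6% and 14%. This assumes 18 per group, r = 0.50, equal SDs at the two visits and no baseline covariate.

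The documents do not establish that T0 is tested in arm-specific slots, or that reordering would balance the groups. The disagreement between random assignment (Sections 2.2 and 2.4.1) and parental choice of schedule (Section 2.1) is a separate matter. The order of T0 deserves correction whichever of the two is meant, because the correction is cheap.

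**What to change.** In Section 2.4.1, put the baseline assessment before group allocation. State that T0 (KTK3+, height and weight) is completed and the data locked for all consented children before any child is allocated and before any schedule is linked to a programme. Sections 2.5.1 and 3 at present tie each group to fixed hours, so that link must be left open until T0 is locked. Otherwise a child's chosen schedule already reveals the arm to staff.

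In Section 3, state the hour of T0, and state that each child is tested at the same hour at T0 and T1. A stable time-of-day effect then cancels in the change score. If a child's T0 hour differs from the later training slot, the T1 test should follow the T0 hour.

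The cost is a change in the order of two phases and the booking of T0 sessions before week 1, with no extra children or measurements. Two small downsides follow: families attend T0 before the programme of their schedule is fixed, and some T1 tests may fall outside the child's own training slot.

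If the investigators also want to use T0 to balance the groups, they must first settle whether allocation is random or follows the parents' schedule. Reordering alone does not deliver that.

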#### 2.4.2. Informed Consent

A comprehensive explanation of the study (materials and methods inclusive) by the research leader and the host institution will be provided to allow the participants/family members/tutors to be fully informed. The subject group will be given adequate time to decide about their participation. To do this, the participants, family members, and tutors must sign and deliver an informed consent form.

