### 2.2. Participants

The study sample will be composed of children aged between 6 and 10 years, all of whom are to be active members of an athletics club located in the district of Leiria, Portugal. All the participants will be affiliated with the Portuguese Athletics Federation and covered by sports insurance, which includes protections regarding training sessions and data collection procedures. The selected age range fits into middle childhood, which is a critical period for motor development and the acquisition of fundamental motor skills. This age range aligns with previous research utilizing the KTK3+ battery, which has been validated and normed specifically for children within this developmental window [24,25], and was chosen because children between 6 and 10 years old are typically enrolled in primary school, where structured physical education and motor skill interventions are most effective at promoting motor competence and physical literacy [26,27]. To be eligible for inclusion in the study, the participants must meet the following criteria: (i) be aged between 6 and 10 years; (ii) be officially registered in the Portuguese Athletics Federation; and (iii) provide written informed consent signed by their legal guardians, along with the child’s verbal assent. The exclusion criteria are as follows: (i) any diagnosed physical or intellectual disability; (ii) any medical contraindications to physical exercise; (iii) failure to obtain parental consent; (iv) failure to complete the entire assessment protocol; (v) failure to complete a minimum of 80% attendance at training sessions in general and, in IG_B, failure to also complete a minimum of 80% attendance at complementary motor activities training sessions; and (vi) being outside the stipulated age range. The children meeting all the eligibility criteria will be randomly assigned to one of the two intervention groups, as described in the study design: (i) Intervention Group A (IG_A) or (ii) Intervention Group B (IG_B).

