##### Intervention Group A (IG_A) Training Program

Intervention Group A (IG_A) will participate in structured athletics training sessions three times per week, each lasting 60 min. The sessions will be held at the Municipal Stadium of Leiria—[name]—on Tuesdays and Thursdays from 17:30 to 18:30, and on Saturdays from 09:00 to 10:00. The structure of each session will follow a consistent format. (i) Warm-up (5 min): Dynamic stretching or light jogging. (ii) Main phase (45 min): Focused athletics training targeting specific objectives—technique, speed, strength, and endurance. (iii) Cool-down (5 min): Static stretching or light jogging. The participants in this group will engage exclusively in athletics training, with no additional activities. The detailed 12-week training program is presented in Table 1.

Training Components OverviewRunning and technique Training

This component focuses on enhancing the biomechanics and efficiency of running. Exercises include drills with and without equipment (e.g., cones, hurdles, pins, and ropes) to promote better posture, stride mechanics, and coordination.

Speed Training

Speed sessions emphasize velocity over short distances (10–30 m), reaction starts, and agility circuits. Activities include varied start positions (sitting, lying), slalom runs, and hurdle sprints to improve explosive acceleration and coordination.

Strength Training

Strength development will be primarily based on bodyweight resistance exercises (e.g., planks, squats, and jumping jacks) and light resistance tools (e.g., 1–2 kg medicine balls, ropes, and kettlebells). Training will follow a circuit-based format using Tabata intervals (20 s work, 10 s rest). Each session will include 4–5 rounds of 4 exercises, with 2 min rests between rounds, focusing on proper technique, functional strength, and muscular endurance.

Resistance Training

Endurance activities will be integrated through continuous running (12–15 min) and structured motor games (e.g., relays, object transport tasks, and team challenges). Given children’s limited motivation for isolated endurance drills, the activities are designed to be engaging and enjoyable, promoting a long-term affinity for aerobic exercise.

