##### Intervention Group B (IG_B) Training Program

Intervention Group B (IG_B) will be engaged in three weekly training sessions, each lasting 60 min. The sessions will take place at the Municipal Stadium of Leiria—[name]—on Tuesdays and Thursdays from 18:30 to 19:30, and on Saturdays from 10:00 to 11:00. This group will follow a blended training approach: (i) two sessions per week (Tuesdays and Saturdays) focused on athletics, replicating the exact training content as IG_A; (ii) one weekly session (Thursdays) dedicated to complementary motor activities, alternating between gymnastics, handball, swimming, and motor games. The complementary session is strategically scheduled for Thursdays, a day with normally higher attendance and positioned between the two athletics sessions, to ensure optimal participation and recovery. A detailed breakdown of the 12-week program is provided in Table 2.

*Training Objectives*

The IG_B program is designed to evaluate the impact of combined athletics and multi-sport exposure on motor competence development. This group will receive the same foundational athletics training as IG_A, but with an added component of diversified motor experiences. The goal is to determine whether this combined training model will provide greater MC benefits than an athletics-only approach.

*Complementary Activities*

*Gymnastics and handball*

These sessions will emphasize foundational movement skills (FMSs) rather than technical sport-specific mastery. The intent is to expose participants to a variety of motor patterns through basic posture, balance, coordination, object manipulation, jumping, and rolling tasks. In handball, an emphasis will be placed on ball handling, passing, receiving, and spatial awareness, helping to enrich motor diversity.

*Swimming*

In week 10, swimming will be introduced to develop aquatic motor skills, including propulsion and object manipulation in water. This aims to broaden the scope of physical literacy and neuromuscular adaptation through exposure to aquatic environments.

*Motor games*

Motor games will be employed to stimulate key motor competencies, such as locomotion, coordination, balance, and object manipulation. These games are intentionally chosen for their educational value and children’s familiarity with them, ensuring engagement and effective skill acquisition. Activities will include cooperative games, relay formats, object transport tasks, and dynamic obstacle circuits.

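### The plan hides from parents which programme runs in which slot, but this conflicts with a consent step that explains materials and methods in full and with a timetable already fixed by arm

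*Protocol article*

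**What the plan says.** All references are to the protocol article.

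- **Section 2.1, Study Design.** The arm follows the parents' choice of timetable: "The participants will be ecologically assigned into one of two intervention groups, depending upon the training schedule chosen by their parents". Families make that choice "being given no prior indication of which of the two programs will function on which schedule".
- **Section 2.2, Participants.** To be included, a child must "provide written informed consent signed by their legal guardians, along with the child’s verbal assent". Children who meet the eligibility criteria are then assigned to a group.
- **Section 2.4.2, Informed Consent.** "A comprehensive explanation of the study (materials and methods inclusive) by the research leader and the host institution will be provided", in order "to allow the participants/family members/tutors to be fully informed". No exception is made for the timetable by arm.
- **Section 2.5.1, Training Programs.** IG_A trains "on Tuesdays and Thursdays from 17:30 to 18:30, and on Saturdays from 09:00 to 10:00"; IG_B trains "on Tuesdays and Thursdays from 18:30 to 19:30, and on Saturdays from 10:00 to 11:00". Section 3 repeats the weekday hours for the post-intervention tests (IG_A 17:30, IG_B 18:30).
- **Section 2.4.1, Procedures.** Phase (iii), before allocation in phase (v), is promotion: "communication strategies will be employed to inform and engage the stakeholders, including the parents, coaches, and athletics club, about the program’s purpose and benefits".

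**The concern.** When the arm follows from a slot the family picks, the comparison is protected from choice by programme only if the family does not know what the slot contains. Section 2.1 recognises this and withholds the link. Section 2.4.2 then promises an explanation that, read literally, includes the link, because the hours of each arm are part of the methods.

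If families know the link when they choose, those attracted to the enriched programme can pick the IG_B slot. If they have already picked a slot when they learn it, they can decline to consent. Either way, the children in the two arms may differ in motivation or expected progress for reasons unrelated to training, and the group-by-time comparison absorbs that difference. The stated 1:1 ratio would also be at risk.

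**Working it through.** **1. The texts side by side**

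| Question | Section 2.1 | Sections 2.4.2 and 2.5.1 |
|---|---|---|
| What are families told? | Not which programme runs when | Materials and methods, in full |
| Does a slot-to-programme link exist yet? | Implied, and withheld | Yes, fixed by day and hour for each arm |
| Is anything exempt from disclosure? | The link | Nothing is named |

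Section 2.2 requires signed consent for eligibility and assigns those who are eligible, so on that text the explanation precedes assignment. No section says whether parents name their slot before or after the explanation. If after, the risk is choice of arm. If before, it is refusal by arm. Neither order is safe as written.

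**2. Size, as an illustration only**

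The plan has no figure to reproduce here. Inputs:

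- From section 4: 18 children per group, plus 15%. 18 × 1.15 = 20.7, rounded to 21 per group, or 42 in all.
- From section 4: correlation r = 0.50, so the variance of the change is 2(1 − 0.5) = 1 and the SD of change equals one SD of the score.
- Assumed: a share q of families choose IG_B for its programme, and the rest split evenly between slots.
- Assumed: children of the choosing families gain δ SD more over 12 weeks whichever programme they follow.
- Assumed: there is no true difference between programmes and no cap on slot size.

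Formulas:

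- Share of all children in IG_B = q + (1 − q)/2 = (1 + q)/2.
- Share of choosers within IG_B = q ÷ [(1 + q)/2] = 2q/(1 + q). In IG_A it is zero.
- Bias in the difference in gain = δ × 2q/(1 + q).
- The false-positive rate is the rejection probability of a two-sided 5% two-sample t-test on the gains when the only difference is this bias.

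| q | δ | Bias (SD) | IG_A : IG_B | False-positive rate |
|---|---|---|---|---|
| 0.10 | 0.3 | 0.3 × 0.2/1.1 = 0.05 | 19 : 23 | 5.3% |
| 0.10 | 0.5 | 0.5 × 0.2/1.1 = 0.09 | 19 : 23 | 5.9% |
| 0.25 | 0.3 | 0.3 × 0.5/1.25 = 0.12 | 16 : 26 | 6.6% |
| 0.25 | 0.5 | 0.5 × 0.5/1.25 = 0.20 | 16 : 26 | 9.4% |
| 0.50 | 0.5 | 0.5 × 1/1.5 = 0.33 | 10 : 32 | about 15% |

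**3. Group size**

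IG_A falls below 18 of 42 when IG_B exceeds 24. At q = 0.25, P(Binomial(42, 0.625) > 24) = 0.71. The reference at q = 0, when slots fill evenly by chance, is P(Binomial(42, 0.5) > 24) = 0.14.

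**The case against.** The strongest reply is that section 2.1 is the specific rule and section 2.4.2 a general consent paragraph. A consent talk can describe both programmes and both timetables and hold back only which goes with which. Publishing the hours in an article is not the same as telling parents. This stands in part. A reader might infer that the concealment is in fact undone, but no section says the link is disclosed at consent. What the documents support is a conflict between two instructions, with nothing in the text to resolve it.

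Four other inferences go beyond the documents:

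- *Coaches choose the arm.* Section 2.1 gives the choice to parents, according to availability. The main researcher is an athletics coach, and staff who know a fixed timetable could steer families. That is a risk, not a stated fact.
- *Promotion reveals the link.* Phase (iii) concerns the programme's purpose and benefits and does not mention slots.
- *Families certainly pick the slot after the explanation.* Section 2.2 orders consent and assignment, but not consent and slot choice.
- *Withholding the link is the only safeguard claimed.* Sections 2.2 and 2.4.1 also assert random assignment, though they describe no mechanism and section 2.1 contradicts them. Genuine individual randomisation would make the present point moot. Merely relabelling the trial as non-randomised would not.

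The illustration is also one-sided. All choosers are sent to IG_B, although every child belongs to an athletics club and some families may prefer athletics alone. The choosers are assumed to gain more, not just to start higher; a higher start alone would not bias the group-by-time term in this way. Slot caps, which the 1:1 ratio may imply, would remove the imbalance in numbers. These objections stand, so the figures show a possible range and are not estimates.

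**Conclusion.** The concern holds as a conflict that the plan should resolve. Withholding the slot-to-programme link (section 2.1) is at odds with explaining materials and methods in full (section 2.4.2) while the timetable by arm is fixed in that same part of the article (section 2.5.1). As written, families could choose or decline by programme, and staff who know the timetable could influence them.

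This conclusion rests on the text alone. The size rests on assumed q and δ. It ranges from negligible (0.05 SD, a false-positive rate of about 5.3%) to material (0.33 SD, about 15%), and the documents do not show where in that range the trial would fall. The change is worth making because it is cheap and allows full consent and concealment to hold together.

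**What to change.** Reconcile sections 2.1 and 2.4.2, and stop fixing the slot-to-programme link in advance:

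1. At consent and in promotion, describe both programmes and both timetables, and say that programmes will be allotted to slots by lot.
2. Have parents commit to a slot in writing, then close the list.
3. Only then have someone outside the coaching team make one random draw of which slot runs IG_A and which IG_B.
4. In sections 2.5.1 and 3, replace the hours by arm with slot 1 and slot 2, programme assigned by draw.

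Nobody can then disclose or exploit a link that does not yet exist, and families are still told everything there is to know.

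The cost is one draw, revised consent wording with notification to the ethics committee, and later notice to coaches. Pool and hall bookings for the complementary session must suit either slot.

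The draw removes selection by programme only. Families who can attend early may still differ from those who can attend late, and a single draw of two slots cannot balance that. State it as a limitation. The claims of random assignment in sections 2.1, 2.2 and 2.4.1 need their own reconciliation with assignment by parental choice.
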